| CT liver:spleen attenuation ratio |   | X |   |   |   |   | X |   |
| Drug dispensation                 |   | X | X | X | X | X |   |   |

- 1 Wk 4 visit only for individuals receiving maraviroc. Bloods are unfasted.
- 2 HR, RR, Temp, BP, Lying and standing BP (postural BP at screening only and to be repeated if history indicates)
- 3 Height only at screening; weight and waist circumference at every visit except week 4
- 4 Symptom directed physical examination only
- 5 Point of care urine dip for haematuria, proteinuria, glycosuria, leucocytes and nitrites
- 6 If no result within the preceding 24 weeks
- 7 Haemoglobin, white cell count and differential, eosinophils, platelets
- 8 Sodium, potassium, chloride, creatinine, urea, alanine aminotransferase (ALT), aspartate aminotransferase (AST), bilirubin, alkaline phosphatase (ALP), gamma glutamyltransferase (GGT), albumin, phosphate, CK, glucose (screening, weeks 4, 24 and 72); lipids (total cholesterol, HDL, LDL, triglycerides) (weeks 24 and 72 only)
- 9 Fasting glucose and fasting lipids (total cholesterol, HDL, LDL, triglycerides)
- 10 HbA1c
- 11 anti-HCV Ab, HCV RNA or HCV antigen, HBsAg; if no prior record of result: anti-HBcAb. HIV Ab/Ag only if no previous documented result
- 12 If no previous record of result: INR, ferritin, caeruloplasmin, copper, thyroid function, alpha-1 antitrypsin, anti-mitochondrial antibodies, anti-nuclear antibodies, anti-smooth muscle antibody, anti-liver/kidney/microsomal antibodies-1, coeliac serology
- 13 If no previous imaging (US, CT, MRI) or liver biopsy result confirming fatty liver in the preceding 24 weeks. This may be performed at any point between the screening and baseline visits.
- 14 Includes both median stiffness and controlled attenuation parameter scores. This may be performed at any point between the screening and baseline visits. For the week 48 and 96 week visits, to be performed within 7 days of the study visit.
- 15 Optional. To be performed within 7 days of the study visit. Preference is for the 7 days prior to baseline.
- 16 Only for individuals assigned to the maraviroc group

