### 3.3 Outcome measures/endpoints

#### **Primary endpoint:**

The primary objective will be assessed with respect to the following measures:

- a) Proportion of eligible individuals approached who are successfully recruited
- b) Monthly participant recruitment rate
- c) Participant retention in the study at 48 and 96 weeks in the maraviroc and non-maraviroc assigned groups
- d) Proportion of participants for whom there is missing data at 48 and 96 weeks in the maraviroc and non-maraviroc assigned groups
- e) Proportion of participants reporting adverse events at 48 and 96 weeks in the maraviroc and non-maraviroc assigned groups
- f) Level of self-reported adherence to the study drug at 48 and 96 weeks in those allocated to the maraviroc group

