## 9. PHARMACOVIGILANCE

### 9.1 Definitions

| Term                         | Definition                                                                                                                                                                                                                                                                                                                                                                                                                                                                                                                                                                                                |
|------------------------------|-----------------------------------------------------------------------------------------------------------------------------------------------------------------------------------------------------------------------------------------------------------------------------------------------------------------------------------------------------------------------------------------------------------------------------------------------------------------------------------------------------------------------------------------------------------------------------------------------------------|
| Adverse Event (AE)    | Any untoward medical occurrence in a participant to whom a medicinal product has been administered, including occurrences which are not necessarily caused by or related to that product.                                                                                                                                                                                                                                                                                                                                                                                                                 |

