## 9.2 Adverse Events and Toxicity Management

Adverse events observed by the Investigator, or reported by the subject, and any remedial action taken, will be recorded in the subject’s eCRF and should be verifiable in the subject’s notes throughout the study. The nature of each event, date of onset, duration and severity will be documented together with the Investigator’s opinion of the causal relationship to the treatment (unrelated, unlikely, possible, probable, and definite).

All subjects experiencing adverse events, whether considered associated with the use of the study medication or not, must be monitored until the symptoms subside and any clinically relevant changes in laboratory values have returned to baseline, or until there is a satisfactory explanation for the changes observed.

Procedures such as surgery should not be reported as adverse events. However, the medical condition for which the procedure was performed should be reported if it meets the definition of an adverse event. For example, an acute appendicitis that begins during the adverse event reporting period should be reported as the adverse event and the resulting appendectomy noted on the eCRF.

Planned procedures such as surgery planned prior to the subject's enrolment into the study need not be reported as adverse events if these are documented as planned at the screening visit.

Clinically significant changes in physical examination and blood safety profiles should also be recorded as adverse events.

An adverse event includes:

- An exacerbation of a pre-existing illness
- An increase in frequency or intensity of a pre-existing episodic event or condition
- A condition detected or diagnosed after trial medication administration even though it may have been present prior to the start of the trial
- Continuous persistent disease/symptoms present at baseline that worsen following the start of the trial

An adverse event does **NOT** include:

- Medical or surgical procedures (e.g. surgery, endoscopy, tooth extraction, transfusion); the condition that leads to the procedure is an AE.
- Pre-existing disease or conditions present at the start of the trial that do not worsen.
- Situations where an untoward medical occurrence has not occurred (e.g. hospitalisations for cosmetic elective surgery/social/convenience admissions).
- HIV-associated conditions or signs/symptoms associated with such conditions unless more severe than expected for the subject's condition.

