### **9.3 Recording and reporting of AEs, ARs, SAEs, SARs AND SUSARs**

All AEs, ARs, SAEs, SARs and SUSARs will be documented in the eCRF.

The adverse event reporting period will be from consent until the subject's final study visit. In addition, any untoward event that may occur subsequent to the reporting period that the Investigator assesses as possibly, probably or definitely related to the study drug medication will also be reported as an Adverse Reaction.

AEs, ARs, SAEs, , SARs and SUSARs may be directly observed, reported spontaneously by the subject or by questioning the subject at each study visit. These will be followed up until they are resolved or the

subject's participation in the study ends (i.e. until the final eCRF is completed for that subject). In addition, all serious adverse events assessed by the Investigator as possibly related to the investigational medication should continue to be followed even after the subject's participation in the study is over.

Such events should be followed until resolution, or until no further change can reasonably be expected. Deaths occurring more than 30 days after the final dose, which are considered to be unrelated to the study medication, should not be reported as a Serious Adverse Event.

SAEs should be reported immediately to the BSCTU.

All **SAEs** occurring from the time of **consent** until **30** days post cessation of trial treatment must be recorded on the SAE Form and emailed to the BSCTU immediately at [[contact]](mailto:[contact]), at least **within 24 hours** of the research staff becoming aware of the event.

For each **SAE** the following information will be collected:

- full details in medical terms and case description
- event duration (start and end dates, if applicable)
- action taken
- outcome
- seriousness criteria
- causality (i.e. relatedness to trial drug / investigation), in the opinion of the investigator
- whether the event would be considered expected or unexpected in relation to the Reference Safety Information.

Any change of condition or other follow-up information should be emailed to the Sponsor as soon as it is available or at least within 24 hours of the information becoming available. Events will be followed up until the event has resolved or a final outcome has been reached.

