| Blood and lymphatic system disorders                                    | Anaemia                                                                                                                                                                             | common                  |
|                                                                         | Pancytopenia, granulocytopenia                                                                                                                                                      | rare                    |
| Metabolism and nutrition disorders                                      | Anorexia                                                                                                                                                                            | common                  |
| Psychiatric disorders                                                   | Depression, insomnia                                                                                                                                                                | common                  |
| Nervous system disorders                                                | Seizures and seizure disorders                                                                                                                                                      | uncommon                |
| Cardiac disorders                                                       | Angina pectoris                                                                                                                                                                     | rare                    |
| Vascular disorders                                                      | Postural hypotension                                                                                                                                                                | uncommon                |
| Gastrointestinal disorders                                              | Abdominal pain, flatulence, nausea                                                                                                                                                  | common                  |

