### 10.3.2 Feasibility Outcome analyses

All analyses will be performed on available cases according to intention to treat (ITT) principles. Therefore, all individuals randomised within the study (including those subsequently withdrawn) will be included in outcome analyses.

The following analyses will be presented:

- a) Proportion of eligible individuals approached who are successfully recruited  
It is envisaged that a recruitment rate of at least 50% will be achieved. This takes into account the likelihood that a proportion of potential recruits will decline particularly owing to the requirement for twice daily pill taking.
- b) Monthly participant recruitment rate. This is expected to be a minimum of at least 2 participants consistently per month, with an average of 3-4.
- c) Participant retention in the study at 48 and 96 weeks in the maraviroc and non-maraviroc assigned groups. This is expected to be at least 65% (cf 35% discontinuation in the MOTIVATE study [9]).
- d) Proportion of participants for whom there is missing data at 48 and 96 weeks in the maraviroc and non-maraviroc assigned groups. This is expected to be less than 20% for all participants.
- e) Proportion of participants reporting adverse events at 48 and 96 weeks in the maraviroc and non-maraviroc assigned groups. This is expected to be less than 10% [18].
- f) Level of self-reported adherence to the study drug at 48 and 96 weeks in those allocated to the maraviroc group. This is expected to be greater than 90%.

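### Primary feasibility item (e) expects under 10% of participants to report adverse events, but the outcome is any-cause and ungraded, so the expectation is very unlikely to be met and says little about the acceptability of maraviroc.

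*Protocol*

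**What the plan says.** Section 3.3 lists as one of six primary measures the "Proportion of participants reporting adverse events at 48 and 96 weeks in the maraviroc and non-maraviroc assigned groups". Section 10.3.2(e) repeats it and adds the expectation: "This is expected to be less than 10% [18". Neither place restricts the count by grade, seriousness or relatedness.

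Section 9.1 defines an adverse event broadly, "including occurrences which are not necessarily caused by or related to that product". Section 9.2 adds worsening of pre-existing illness, and also laboratory and examination findings: "Clinically significant changes in physical examination and blood safety profiles should also be recorded as adverse events". It excludes HIV-associated conditions no worse than expected, laboratory changes without clinical significance, pre-existing disease that does not worsen, and procedures. On timing, Section 9.3 says "The adverse event reporting period will be from consent until" the final study visit. Section 7.1.2 allows screening up to 42 days before randomisation, so events before randomisation fall inside the period.

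Section 9.3 also tabulates maraviroc reactions of moderate or greater intensity that occur more often than in the comparator. Several are classed as common (at least 1/100 and below 1/10), for example "Abdominal pain, flatulence, nausea".

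Table 1 marks symptom and adverse-event review at week 4, and its first footnote reads "Wk 4 visit only for individuals receiving maraviroc. Bloods are unfasted". Section 7.6 describes that visit as a toxicity history, examination if required, and safety bloods.

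**The concern.** The 10% figure and the outcome it is attached to do not appear to describe the same class of event. Almost any intercurrent illness over nearly two years would count, yet the plan expects fewer than one participant in ten to have anything to report.

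This is a primary measure. Section 3.1 says that confirmed feasibility and acceptability will support a larger placebo-controlled trial. If the observed proportion exceeds 10% mainly because of unrelated or mild events, the comparison with the expectation tells the designers of the next trial little about whether maraviroc is acceptable.

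The second, smaller matter is that the outcome is reported by arm in an open-label trial while one arm has an additional scheduled search for events.

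**Working it through.** **Is there a figure to reproduce?** No. The 10% rests only on reference 18. Section 1 describes that study as cenicriviroc versus efavirenz in people not previously treated, with liver markers at baseline and 48 weeks, and quotes no adverse-event rate from it. The check is therefore one of plausibility.

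**Inputs from the protocol.** 30 per arm (Section 10.1: 20 analysed, 33% attrition, 20/0.67 = 29.9, rounded to 30). Time points are 48 weeks = 48 × 7/365.25 = 0.920 years and 96 weeks = 1.840 years. Eleven reactions are classed as common: anaemia, anorexia, depression, insomnia, abdominal pain, flatulence, nausea, ALT increased, AST increased, rash and asthenia.

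**Assumptions.** The any-cause risk is not given, so a range is used. "At" the visits is read as cumulative up to them.

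**Step 1: what under 10% allows.** 3/30 is exactly 10%, so at most 2 of 30 in an arm (1 of 20 after the assumed attrition; 5 of 60 overall).

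**Step 2: the implied event rate.** With a constant rate r, the proportion with at least one event by time t is 1 − exp(−rt). Setting this to 0.10 gives r = −ln(0.9)/t = 0.1054/t.

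- 48 weeks: 0.1054/0.920 = 0.115 per person-year, one first event per 8.7 person-years.
- 96 weeks: 0.1054/1.840 = 0.057 per person-year, one first event per 17.5 person-years.

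| Assumed first-event rate per person-year | By 48 weeks | By 96 weeks |
|---|---|---|
| 0.05 | 4.5% | 8.8% |
| 0.1 | 8.8% | 16.8% |
| 0.2 | 16.8% | 30.8% |
| 0.5 | 36.9% | 60.1% |
| 1 | 60.1% | 84.1% |

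**Step 3: the protocol's own reaction table.** If k reactions each have probability q and are independent, the chance of at least one is 1 − (1 − q)^k.

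- k = 11, q = 0.01 (the lower bound of the class): 1 − 0.99^11 = 10.5%.
- k = 10, q = 0.01 (ALT and AST counted once): 1 − 0.99^10 = 9.6%.
- k = 11, q = 0.02, 0.03 and 0.05: 19.9%, 28.5% and 43.1%.

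If all the terms fell in the same people, the floor would be 1%. These figures leave out Grade 1 events, uncommon reactions and everything unrelated to the drug.

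**Step 4: chance of observing under 10% in an arm of 30.** This is P(X ≤ 2) for X ~ Binomial(30, p). At p = 0.2: 0.8^30 + 30(0.2)(0.8^29) + 435(0.04)(0.8^28) = 0.0012 + 0.0093 + 0.0337 = 0.044.

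| True risk (assumed) | P(at most 2 of 30) |
|---|---|
| 5% | 0.81 |
| 10% | 0.41 |
| 15% | 0.15 |
| 20% | 0.044 |
| 30% | 0.002 |

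**Step 5: ascertainment.** Scheduled post-baseline reviews are at weeks 4, 24, 48, 72 and 96 on maraviroc (five) and at weeks 24, 48, 72 and 96 on control (four). This is a count of visits. The protocol gives nothing from which to turn it into a size of bias.

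**The case against.** The strongest reply is that the protocol gives no any-cause rate. A reader might infer from the tables above that the expectation cannot be met. The documents do not show that: at a true risk of 5% an arm of 30 would come in under 10% with probability 0.81. The reaction table does not settle it either, since overlap between terms pulls the result below 10% and the listed frequencies are not exposure adjusted. This part of the reply stands, and very unlikely is the most that can be said.

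A reader might also infer that both arms must fail. The reaction table concerns maraviroc recipients only. For the control arm the argument rests on the breadth of the definition and the length of follow-up, with an assumed rate.

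Nor is the 10% a pass/fail rule. Section 10.3.2 says only that it is expected, and the proportions by arm remain informative whatever was expected. It would be too strong to say that the outcome carries no information; the weakness lies in the benchmark.

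The wording also leaves room for a milder reading. Section 3.3 uses at for the primary measures and by for most secondary ones, so status at the visit may be meant, which would be easier to satisfy. That ambiguity is itself worth removing.

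On week 4, Section 10.3.2 specifies no between-arm contrast for adverse events. Control participants can report early events spontaneously or at week 24, and onset dates are recorded. The extra visit changes a cumulative proportion only for someone whose sole event would otherwise have been missed, most plausibly a transient laboratory change. A material bias against maraviroc is therefore not established.

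**Conclusion.** The point holds in a limited form. Item (e) attaches an underived expectation of under 10% to an any-cause, ungraded outcome collected from consent to the final visit. On the cumulative reading it allows 2 of 30 per arm and needs first events rarer than about one per 17.5 person-years at 96 weeks. The protocol's own common reactions put the maraviroc arm at about 10% at their lower bounds (10.5% if independent, 9.6% with ALT and AST counted once), before mild or unrelated events are added. With assumed true risks of 10%, 20% and 30%, the chance of meeting the figure in an arm is 0.41, 0.04 and 0.002. The expectation is therefore very unlikely to be met and, as a yardstick for a primary outcome, says little about the acceptability of maraviroc.

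The conclusion rests on the cumulative reading and on any-cause risks that the protocol does not supply. The unequal week-4 ascertainment, five scheduled reviews against four, is real but secondary, and its effect cannot be sized.

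**What to change.** Reword item (e) in Section 10.3.2, and the matching measure in Section 3.3, as follows.

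- Tie the benchmark to a defined class of events with onset after randomisation that is recorded in both arms, for example Grade 3 or worse on the Appendix 2 scale. Report events leading to maraviroc discontinuation for the maraviroc arm only, because that category has no meaning in a control arm without study drug.
- State the source of the percentage for that class. The present 10% should not simply be carried over.
- State that the proportion is cumulative to weeks 48 and 96.
- Report the any-event proportion by arm descriptively, with no 10% expectation.

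For week 4, add a by-arm sensitivity table that leaves out events identified solely through that visit's scheduled bloods or examination. Keep symptomatic events that controls could equally report at week 24; dropping those as well could tilt the comparison in favour of maraviroc. Keep all week-4 findings in the maraviroc safety listing.

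The cost is a rewording, one extra table and possibly one eCRF field. Section 9.2 already requires onset date, duration, severity and causality, but it does not list how or at which visit an event was detected, so that should be confirmed first.

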| Primary                            | Assessment of the feasibility and acceptability of the addition of maraviroc to OBT for the treatment of NAFLD in people living with HIV                                                                             | 
Proportion of eligible individuals approached who are successfully recruited
 
Monthly participant recruitment rate
 
Participant retention in the study at 48 and 96 weeks in the maraviroc and non-maraviroc assigned groups
 
Proportion of participants for whom there is missing data at 48 and 96 weeks in the maraviroc and non-maraviroc assigned groups
 
Proportion of participants reporting adverse events at 48 and 96 weeks in the maraviroc and non-maraviroc assigned groups
 
Level of reported adherence to the study drug at 48 and 96
 |

|           |                                                                                                                                                                                                                                                                                                                                                                                                                                                                                                                                                                                                                                                                                                       |                                                                                                                                                                                                                                                                                                                                                                                                                                                                                                                                                                                                                                                                                                                                                                                                                                                                                                                       |

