## 3 OBJECTIVES AND OUTCOME MEASURES/ENDPOINTS

### 3.1 Primary objectives

The primary objective will be to assess the feasibility and acceptability of the addition of maraviroc to OBT, versus maintenance of OBT alone, in the treatment of NALFD in people living with HIV. This will be assessed with respect to the following:

- a) Acceptability of recruitment into the study to eligible individuals
- b) Monthly participant recruitment rate
- c) Participant retention rate
- d) Completeness of the data set
- e) Proportion of individuals reporting adverse events
- f) Self-reported adherence to the study drug

The specific time points with respect to the above are provided in the 'primary measures' section below. The finding of confirmed feasibility and acceptability of the treatment approach of addition of maraviroc to effective cART in this population will support the establishment of larger, double-blind, placebo-controlled RCT to assess the efficacy of this intervention definitively.

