## 7.6 Trial assessments

Please see Table 1 for details of the timeline for trial visits and which procedures and assessments will be performed at each visit.

The following are recorded at the baseline visit and then every 24 weeks until the final visit at 96 weeks (i.e. day 1, week 24, week 48, week 72 and week 96):

- history and if necessary symptom-directed examination
- adherence to maraviroc as assessed by (i) self reported adherence through completion of a diary card and (ii) pill counting by pharmacy/research team member.
- weight and BMI
- waist circumference
- liver function, renal function, phosphate, CK, glucose (fasted at baseline, weeks 48 and 96), and lipid profile (fasted at baseline, weeks 48 and 96)(blood draw)
- FBC (blood draw)
- HIV viral load (blood draw)
- Urine dipstick macroanalysis and, for WOCBP, pregnancy testing

The following are recorded at the baseline visit and then every 48 weeks until the final visit at 96 weeks (i.e. day 1, week 48 and week 96):

- CD4/CD8 cell count and % (blood draw)
- HbA1c (blood draw)
- ELF score (blood draw)
- CLDQ:NAFLD questionnaire
- SF-36 questionnaire
- WPAI-SHP questionnaire
- Dietary and exercise history

The following is recorded at screen, week 48 and week 96:

- Fibroscan. For screening, the Fibroscan may be performed up to 42 days prior to baseline. For the week 48 and 96 visits this may be performed within 7 days of the study visit.

The following **optional investigation** will be performed at the baseline visit and at the 96 week visit:

- CT liver : spleen attenuation ratio. This may be performed within 7 days of the study visit with preference for the 7 days prior to baseline.

An additional week 4 safety visit will be required for those individuals in the maraviroc group, with the following procedures being performed:

- assessment of any drug toxicity through targeted history and, if required, examination
- liver function, renal function, CK, phosphate, glucose, full blood count (blood draw)
- HIV viral load (blood draw)

The following will be performed at screening only (if no hepatic imaging or liver biopsy result is available in the preceding 24 weeks):

- USS liver

The following will be performed at baseline only (if not available in the preceding 24 weeks):

- CCR5 tropism (blood draw)

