### 8.11 Assessment of compliance

Aim: To describe how compliance will be assessed

Participant adherence to MVC will be assessed through:

- a) Self reporting of doses of MVC taken via a diary card
- b) Pill counting at each visit by a pharmacist/research team member and recording of the number of pills returned

Participants will bring in all pill bottles at each study visit. The total number of IMP pills remaining at each visit will be counted and, then returned to the participant to take until the bottle is finished.

The percentage of IMP compliance for each participant will be calculated. Where this figure is <80%, this will lead to likely withdrawal from the study although this will be at the discretion of the PI. Where a discrepancy exists between self reported compliance and compliance identified via pill counting, any decision to withdraw the participant will rest with the study PI.

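### Primary adherence measure (f) is reported from self-report alone, although a pill count is also recorded, so over-reporting in the diary would not show in the feasibility result

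*Protocol*

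**What the plan says.** Three sections of the protocol define the adherence component of the primary objective as self-report. Section 3.1 (f) lists "Self-reported adherence to the study drug". Section 3.3 (f) and Section 10.3.2 (f) both specify "Level of self-reported adherence to the study drug at 48 and 96 weeks in those allocated to the maraviroc group". Section 10.3.2 adds "This is expected to be greater than 90" per cent. The Trial Summary is slightly looser, with "Level of reported adherence to the study drug at 48 and 96" weeks, but it names no pill count either.

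The protocol also collects a second measure. Section 7.6 assesses adherence by a diary card and by "pill counting by pharmacy/research team member", and repeats both kinds of measure at early termination. Section 8.11 asks for "Pill counting at each visit by a pharmacist/research team member and recording of the number of pills returned", says that the tablets counted go back to the participant, and has a compliance percentage calculated for each participant. It then states "Where this figure is <80%, this will lead to likely withdrawal from the study although this will be at the discretion of the PI". Its last provision begins "Where a discrepancy exists between self reported compliance and compliance identified via pill counting", and leaves any resulting withdrawal decision to the site's principal investigator.

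**The concern.** The staff count is recorded and turned into a percentage, yet no primary or secondary outcome uses it. The only adherence figure in the feasibility result is the one participants give about themselves, which is the source more open to over-reporting. The discrepancy provision in Section 8.11 governs whether a participant stays in the study. It does not say how a discrepancy is shown in the results.

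Little else in the protocol would reveal missed maraviroc. Participants enter with suppressed viral load on their existing regimen (Sections 6.1 and 8.12), so viral load need not respond to missed maraviroc doses. The blood samples listed in Section 7.8 include no maraviroc level. The pill count is therefore the main check on the diary.

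At stake is what the pilot tells the designers of the next trial. Section 3.1 says that confirmed feasibility and acceptability will support a larger placebo-controlled trial, and Section 10.3.2 (a) itself names twice-daily pill taking as a likely reason for declining. An adherence figure that is too high would make that burden look lighter than it is.

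**Working it through.** **1. Where each measure is used**

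| Place in protocol | Diary / self-report | Pill count |
|---|---|---|
| 3.1 (f), objective | yes | no |
| 3.3 (f), endpoint | yes | no |
| 10.3.2 (f), analysis and >90% expectation | yes | no |
| 7.6, assessments | collected | collected |
| 8.11, compliance | collected | collected; a compliance percentage is calculated |
| 8.11, discrepancy provision | withdrawal decision only | withdrawal decision only |

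Section 8.11 does not say whether the percentage compared with 80% comes from the diary or the count.

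**2. The plan's own figure.** The >90% is a stated expectation with no formula or source, so there is nothing to reproduce.

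**3. Scale of the expectation.** With the twice-daily schedule of Section 8.6, 48 weeks is 48 × 7 × 2 = 672 doses and 96 weeks is 96 × 7 × 2 = 1344 doses. Ten per cent of these is about 67 and 134 missed doses. This only gives the scale; it says nothing about over-reporting.

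**4. Effect of over-reporting (assumed, because the documents give no value).** Adherence by count = diary adherence − over-report, in percentage points.

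| Diary mean | 0 points | 5 points | 10 points | 15 points |
|---|---|---|---|---|
| 91% | 91% | 86% | 81% | 76% |
| 95% | 95% | 90% | 85% | 80% |

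With no over-report the two measures agree. With a diary mean of 91%, any over-report of 1 point or more takes the count to 90% or lower. With a diary mean of 95%, it takes 5 points.

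**5. A few participants are enough.** Assume 20 evaluable maraviroc participants (the per-group number for analysis in Section 10.1), all with 95% in the diary. Suppose k of them have a 60% count and the rest 95%.

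- Mean by count = (60k + 95(20 − k)) / 20
- k = 2: (120 + 1710) / 20 = 91.5%
- k = 3: (180 + 1615) / 20 = 89.75%

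The diary mean stays at 95% in both cases. Three discordant participants out of 20 would put the two measures on opposite sides of 90%, and the planned result would not show it.

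**The case against.** The strongest reply is that nothing here is contradictory. Self-report is specified consistently, the objective is feasibility and acceptability, and a participant diary is a defensible way to measure that. The pill count has its own stated purpose in monitoring compliance, and a statistical analysis plan that is not shown could tabulate it. The consistency is real, and it makes this a matter of improvement, not of error. It does not dispose of the point: a later plan could add a supporting table, but the protocol itself fixes the primary measure and its expectation on one source.

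Several stronger readings are tempting, and the documents do not support them.

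- A reader might infer that the protocol expects the two measures to disagree. Section 8.11 is conditional: it provides for a discrepancy and does not predict one.
- A reader might infer that a favourable diary figure with a poor count proves the drug was not taken, or that a good count proves it was. A count shows tablets gone from the bottle, not tablets swallowed.
- A reader might infer that measure (f) is the trial's only record of exposure. The counts are also recorded, so the exposure data exist; what is missing is their place in the reported outcome.
- A reader might treat 90% as a go/no-go threshold. Section 10.3.2 states an expectation, and no progression rule is tied to it.
- A reader might conclude that the 90% figure should move wholly to the pill count. It was set for self-report, and counts will be missing when bottles are not brought back, so that exchange is debatable.

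The absence of blinding adds little to the argument, since participants in a blinded trial also report their own adherence.

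**Conclusion.** The point stands in a limited form. The protocol assesses one of its six primary feasibility measures on self-report only and leaves a recorded cross-check out of every outcome, so over-reporting would go unseen in the result. Whether over-reporting will occur, and how much, cannot be determined from the documents. On the assumed range of 0 to 15 points, a reported 91% would be 76% to 91% by count: no effect at one end, and below the 80% compliance line of Section 8.11 at the other. The 20-participant example rests on assumed discordant values and shows only how few would be needed. The trial's validity is not in question; this is an inexpensive change that makes measure (f) more informative.

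**What to change.** In Sections 3.3 (f) and 10.3.2 (f), keep the diary figure and report pill-count adherence beside it at weeks 48 and 96:

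- Define adherence by count as (tablets dispensed − tablets remaining) / tablets expected for the prescribed dose over the same period. Because Section 8.11 hands counted tablets back, carry these over to the next interval so that they are not treated as taken.
- Show both figures against the 90% expectation, and state that the expectation was set for self-report.
- Report the difference between diary and count, and the number of participants with no usable count.
- Describe the count as a cross-check and not as proof of ingestion.

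Align Section 3.1 (f) and the Trial Summary with this wording. Two passages also need reconciling by the sponsor. Section 8.11 should say which source its compliance percentage uses. The count is described there as taken at each visit, whereas Section 7.6 lists adherence at baseline and every 24 weeks and does not list it for week 4. Both descriptions cover weeks 48 and 96, so the proposed reporting does not depend on the answer.

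No new data collection is needed. The cost is an amendment of wording, which the sponsor must classify under Section 13.9, together with a possibly less favourable adherence figure and some missing counts.
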